
In line with findings in adult AN patients it is hypothesized that adolescents with AN will show more pronounced negative cognitive biases compared to healthy adolescents (HC group) for both ED-related information (hypothesis 1a) [e.g., 11, 12, 20] and non-ED-related information (hypothesis 2a) [e.g., 22, 29]. Furthermore, it is expected that adolescents with AN will show stronger biases for ED-related information than adolescents with depression or anxiety disorders (hypothesis 1b), whereas biases for non-ED-related stimuli will be similar or less pronounced in adolescents with AN compared to adolescents with depression or anxiety disorders (hypothesis 2b). Adolescents with depression or anxiety disorders (CC group) are not expected to differ from the HC group regarding ED-related biases (hypothesis 1c) but to show more pronounced negative biases for non-ED-related information than the HC group as well (hypothesis 2c) [in line with e.g., 47, 48]. In summary, for ED-related biases we expect the following pattern: AN > CC = HC (hypothesis 1) and for non-ED-related biases we expect: CC ≥ AN > HC (hypothesis 2). Thus, we expect specificity of biases to translate into differential results for the two types of content (i.e., Group × Content interactions in the analyses). In addition, we will explore to what extent cognitive biases are associated with participants’ psychopathology.

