### Participants

A total of 105 girls aged 12–18 years will be included in the study: 35 patients with AN, 35 clinical controls (patients suffering from a depressive episode or an anxiety disorder; CC group) and 35 healthy controls (HC group). Due to the gender imbalance with significantly higher prevalence of AN in women than in men [gender ratio female:male approximately 10:1; e.g., 3], only female adolescents are included. Participants are included in the AN group if they meet diagnostic criteria for AN according to DSM-5 [1]. Participants are included in the CC group if they meet criteria for major depression, social phobia, or generalized anxiety disorder according to DSM-5 [as these are the most frequent comorbidities of AN; e.g., 44, 46; and at the same time known to be associated with cognitive biases; e.g., 47] and do not meet criteria for an ED currently or in the past. Participants are included in the HC group if they do not meet criteria for any current or past mental disorder (axis 1 disorders as assessed with a standardized diagnostic interview, see below). Exclusion criteria for all groups are: below average intelligence [IQ < 85; assessed with the CFT 20-R; 62], insufficient German language skills, non-corrected visual impairment, pervasive developmental disorders, psychotic disorders, bipolar disorder, or substance abuse.

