#### Analyses of hypotheses

Statistical analysis of the data will be performed using IBM SPSS Statistics. Group differences in demographic and clinical characteristics (age, IQ, body-mass-index as well as ED, depression, and anxiety symptoms) and other questionnaire scores (self-esteem, body dissatisfaction, and social appearance anxiety) will be examined using univariate ANOVAs with the between-subjects factor Group (3: AN, CC, HC) and follow-up *t*-tests. The hypotheses will be addressed with separate analyses for attention, interpretation, and memory biases. Repeated-measures ANOVAs on bias scores will be performed with within-subject factor Content (2: EDR, NED) and between-subjects factor Group (3: AN, CC, HC). Significant main effects and interactions will be followed up by post-hoc ANOVAs and *t*-tests. We expect our hypotheses (hypothesis 1 regarding ED-related biases: AN > CC = HC; hypothesis 2 regarding non-ED-related biases: CC ≥ AN > HC) to translate as Group × Content interactions in the ANOVAs and corresponding results in the post-hoc tests. Associations between bias scores and psychopathology (questionnaire measures) will be assessed via Pearson’s correlations. For all analyses, the significance level will be set to *p* = 0.05 (two-tailed) and adjusted according to the Bonferroni–Holm procedure [85] when multiple post-hoc comparisons are performed. Effect sizes will be reported for all significant effects: *η*_*p*_^2^ and *η*_*G*_^2^ for ANOVA effects and Cohen’s *d*_*s*_ for between-group *t*-tests, as suggested by Lakens [86]. In addition to testing our hypotheses, we will explore to what extent cognitive biases are related to participants’ psychopathology by calculating correlations between bias scores and ED, depression, and anxiety symptoms as well self-esteem, body dissatisfaction, and social appearance anxiety.

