Major strengths of the study include a thorough diagnostic assessment of all participants, the systematic and comprehensive assessment of cognitive biases addressing multiple levels of information processing as well as the content-specificity hypothesis, and the inclusion of a clinical control group to also address the question of disorder-specificity. Furthermore, an elaborate data processing and analysis strategy has been decided upon beforehand.

Influential publications have underlined the importance of experimentally investigating key processes of psychopathology in EDs [87] and especially AN [88] as this may shed light on the mechanisms that cause and maintain the disorder as well as the mechanisms that need to be targeted in order to change and reduce ED psychopathology. Cognitive biases may be a promising starting point since they are both, presumably involved in the etiology and maintenance of AN [e.g., 8–10], as well as modifiable in experimental settings [e.g., 34, 40, 41, 89–91]. However, as also suggested by Paslakis and colleagues [57], precisely specifying what kinds of cognitive biases characterize patients with AN and investigating the extent to which these biases are related to their psychopathology is an essential precursor for efficiently experimentally modifying biases in this particular population. As attempting to manipulate cognitive biases only makes sense for biases that (1) characterize the target population (in comparison to control groups), (2) are related to their psychopathology, and (3) can be reliably measured, systematic knowledge on biases can help subsequent studies to choose the most promising ones as their interventional targets.

In summary, the present study, which is the first to assess cognitive biases in AN in such a comprehensive way, particularly in adolescents, is likely to advance our knowledge about an important maintaining mechanisms of AN and make a valuable contribution to the field. It will have important implications for cognitive behavioural theories of AN as well as subsequent studies aiming to modify cognitive biases in adolescent AN patients.^5^

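### The exploratory bias–symptom correlations carry no group term, so if pooled over all 105 girls they can arise from group means alone and cannot show an association within AN

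*Protocol article*

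**What the plan says.** The section Analyses of hypotheses fixes the method: "Associations between bias scores and psychopathology (questionnaire measures) will be assessed via" Pearson's correlations. It returns to the aim at the end of the paragraph: "we will explore to what extent cognitive biases are related to participants’ psychopathology by calculating correlations between bias scores" and the symptom, self-esteem and body-image questionnaires. No group factor, covariate or subgroup is attached to these correlations, whereas Group is written out as a factor for every ANOVA in the same paragraph. The work is labelled exploratory and set apart from the hypotheses.

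The Participants section plans "35 patients with AN, 35 clinical controls" and 35 healthy controls. Entry is by diagnosis. For the healthy group: "Participants are included in the HC group if they do not meet criteria for any current or past mental disorder". For the clinical controls: "Participants are included in the CC group if they meet criteria for major depression, social phobia, or generalized anxiety disorder", with no eating disorder now or earlier. The Background then predicts group differences in bias: "for ED-related biases we expect the following pattern: AN > CC = HC (hypothesis 1"), and CC ≥ AN > HC for non-ED-related bias.

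The Discussion says that trying to modify a bias makes sense only if three conditions hold. The first is that the bias distinguishes the target population from controls. The second is listed separately: "2) are related to their psychopathology". The third is reliable measurement.

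**The concern.** When groups are chosen to sit at different levels of one variable and are expected to differ on another, the correlation in the combined sample has two parts: the association inside the groups and the alignment of the group means. Pearson's r over everyone does not separate them. A girl with AN will tend to score higher on the eating-disorder questionnaire than a healthy girl, and, if hypothesis 1 is right, higher on ED-related bias as well. That is enough for a positive pooled r, even if among girls with AN the more symptomatic ones are no more biased.

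This matters because the article treats the group difference and the relation to psychopathology as two separate pieces of evidence for choosing targets in later bias-modification studies. A pooled r draws partly on the first, so it cannot establish the second on its own.

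**Working it through.** **The plan's own figures.** None is given for the correlations. The sample-size figures elsewhere do reproduce. With three groups, two measures (m = 2), α = 0.05 and an assumed correlation of 0.5 between measures (the article states none):

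- Group main effect: f² = 0.08/0.92 = 0.087; noncentrality = f²·N·m/(1 + (m − 1)·0.5) = 0.087 × 87 × 2/1.5 ≈ 10.1; power 0.804 at N = 87.
- Group × Content: f² = 0.03/0.97 = 0.031; noncentrality = f²·N·m/(1 − 0.5) = 0.031 × 81 × 2/0.5 ≈ 10.0; power 0.800 at N = 81.

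Nothing below changes these.

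**Inputs for the correlation check.**

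- Groups of 35/35/35; two-sided α = 0.05 (article).
- Bias effects from the Sample size section: 0.5 (ED-related attention), 0.8 (ED-related memory), 1.5 (the lower bound reported for interpretation). These come from adult samples.
- Group patterns from the Background: AN > CC = HC, and CC ≥ AN > HC taken as equality.
- Assumptions: symptom gap of 1 to 2 SD between the raised and the other groups, unit within-group SDs, normal data, and a true within-group correlation of zero.

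**Formula.** With equal groups and no within-group association,

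r = cov(group means) / √[(1 + var of bias means)(1 + var of symptom means)].

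If one group (or two of three) is raised by d for bias and s for symptoms, the covariance is 2ds/9 and the variances are 2d²/9 and 2s²/9.

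Example, d = 1.5 and s = 2: covariance = 2 × 1.5 × 2/9 = 0.667; variances 0.500 and 0.889; r = 0.667/√(1.500 × 1.889) = 0.667/1.683 = 0.40.

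Example, d = 0.5 and s = 1: 0.111/√(1.056 × 1.222) = 0.111/1.136 = 0.10.

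At N = 105 the critical |r| is 0.192. Rejection rates are from 4,000 simulated studies per scenario. The two patterns agree within about one percentage point; the rates shown are for AN > CC = HC.

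| Bias effect | Pooled r, symptom gap 1 to 2 SD | Pooled test rejects |
|---|---|---|
| 0.3 | 0.06–0.10 | 9–17% |
| 0.5 | 0.10–0.16 | 16–37% |
| 0.8 | 0.15–0.24 | 34–71% |
| 1.5 | 0.25–0.40 | 74–100% |

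After centring both scores at their group means, the average r is 0.00 and the test rejects in 4.5–5.7% of runs across all scenarios, close to the nominal 5%.

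**Less favourable case.** If ED-related bias is raised only in AN while depression is raised in both patient groups, the covariance halves to ds/9. Then r runs from 0.05 (d = 0.5, s = 1) to 0.20 (d = 1.5, s = 2), with rejection in 7–52%.

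**Precision of the alternative.** By Fisher's z, power for a true within-group r of 0.3 (z = 0.3095) is:

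- adjusted for group, N = 105: Φ(0.3095 × √100 − 1.96) = Φ(1.14) ≈ 87%;
- AN group alone, n = 35: Φ(0.3095 × √32 − 1.96) = Φ(−0.21) ≈ 42%.

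**The case against.** The best defence is that pooling is inferred. The article does not name the sample for the correlations, and the Discussion's interest in AN patients would fit an AN-only analysis. A condensed article may leave that choice to a fuller plan. This stands as a caution. However, the text speaks of participants in general, puts Group into every other analysis in the paragraph, and says in the Discussion that the analysis strategy was settled in advance. The method is stated, and as stated it has no safeguard.

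Second, the analysis is exploratory and decides nothing in this study. That is right and limits the weight of the point. The Discussion says only that such knowledge can help later studies choose targets.

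Third, a correlation across the whole sample is a legitimate description if the question is dimensional, and adjusting for group removes symptom variance that is of interest. That also stands, which is why the pooled value need not be dropped. It still does not answer a question about association within AN.

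Some stronger readings are tempting but not supported:

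- A reader might infer that the groups are selected to differ on bias. They are selected on diagnosis only; the bias difference is the hypothesis.
- A reader might infer that every bias with a group difference will appear symptom-related, or that the pooled r merely restates the group difference. At a bias effect of 0.5 most simulated studies do not reject, and where the patterns differ the induced r is modest.
- A reader might add multiplicity: six bias scores by seven questionnaire scores gives 42 tests and 42 × 0.05 ≈ 2 false positives under a global null, with Holm tied to post-hoc comparisons. For correlations already called exploratory, correction is a matter of preference, and the reliability rule may reduce the number of scores. It is not part of this point.

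**Conclusion.** The point holds as a weakness in an exploratory analysis. Read naturally, the planned correlations let group means alone produce an association. Its size depends on the bias effect: slight at 0.3 SD, appreciable at 0.8 SD and dominant at 1.5 SD when symptom and bias share a group pattern; roughly half as large in r when ED-related bias is set against a symptom raised in both patient groups. These figures rest on assumed symptom gaps of 1 to 2 SD, equal within-group SDs, normality, and adult effect sizes that the article itself says may be smaller in adolescents. The conclusion that a pooled r cannot by itself separate the Discussion's second criterion from its first needs only that groups differ in mean on both variables.

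**What to change.** State the analysis set for the correlations. Beside any pooled r, report (a) the group-adjusted correlation, that is, the partial correlation given Group, computed from group-centred scores, and (b) r with a 95% confidence interval separately for AN, CC and HC. Say in advance that statements about whether a bias relates to psychopathology within AN will rest on the adjusted and AN-group estimates and not on the pooled one.

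This changes wording and output only; the data are already planned. The price is precision: with 35 girls the AN estimate has about 42% power for r = 0.3, so it should be read through its interval and not as significant or not. The adjusted estimate at N = 105 has about 87% power for the same value, but it averages over groups, which is why the per-group values belong beside it. If exclusions reduce the sample, both lose some precision.

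### Bonferroni–Holm for pairwise comparisons among three groups is valid but needlessly conservative; a closed test behind each content's own Group ANOVA keeps the 5% bound with more power

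*Protocol article*

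**What the plan says.** Under Analyses of hypotheses, each bias (attention, interpretation, memory) gets its own repeated-measures ANOVA with two content levels (EDR, NED) and three groups (AN, CC, HC). The next step is given as "Significant main effects and interactions will be followed up by post-hoc ANOVAs"; pairwise t-tests are named alongside. The significance level is two-tailed 0.05, "adjusted according to the Bonferroni–Holm procedure [85] when multiple post-hoc comparisons are performed".

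The Background states the two main hypotheses as patterns over the three groups. The first reads "for ED-related biases we expect the following pattern: AN > CC = HC (hypothesis 1"). It needs AN–HC and AN–CC to be significant for EDR (1a and 1b). The second reads "for non-ED-related biases we expect: CC ≥ AN > HC (hypothesis 2"). It needs AN–HC and CC–HC for NED (2a and 2c).

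Two things are left open. The article does not say which comparisons form one Holm family: three pairs within a content, six over both contents, or more. It also does not say that the t-tests for a content require a significant one-way Group ANOVA for that same content.

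**The concern.** Among three means, any two pairwise equalities imply the third. The only intersection null within a content is therefore that all three means are equal, and the one-way Group ANOVA tests exactly that. If that ANOVA must be significant first, the closed-testing principle allows each pair to be tested at the full 0.05. Holm's steps of 0.05/3 = 0.0167 and 0.05/2 = 0.025 are then stricter than strong control requires.

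The loss falls on the quantity that matters. Each pattern hypothesis needs two pairs at once, so the 0.0167 and 0.025 steps both apply. The Sample size section sizes only the Group main effect and the interaction, not the pairwise tests on which the hypotheses rest.

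**Working it through.** **Inputs from the article.** Two-tailed alpha 0.05; three groups; two contents; 35 per group; partial eta squared 0.08 for the Group main effect and 0.03 for the interaction; power 0.80.

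**Assumptions not in the article.** Normal scores with equal variances; correlation 0.5 between a girl's EDR and NED scores; mean patterns (d, 0, 0) for EDR and (d, d, 0) for NED; no exclusions.

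**1. The plan's own figures.** Repeated-measures noncentral F with m = 2 and rho = 0.5:

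- Group effect: f² = 0.08/0.92 = 0.0870; lambda = f²·N·m/(1 + (m−1)·rho) = 0.0870 × 87 × 2/1.5 = 10.09; power 0.804. N = 87 is reproduced.
- Interaction: f² = 0.03/0.97 = 0.0309; lambda = f²·N·m/(1 − rho) = 0.0309 × 81 × 2/0.5 = 10.02; power 0.800. N = 81 is reproduced.

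**2. Effect size for the pairs.** For one group apart from two equal groups, f = d·√2/3. With f = √0.0870 = 0.295, d = 3 × 0.295/√2 = 0.626. Using the main-effect value as an effect within one content is itself an assumption.

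**3. Power for both required pairs in one content** (simulation, 20,000 runs per scenario):

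| n per group | d | Holm over 3 pairs | ANOVA at 0.05, then pairs at 0.05 | Gain |
|---|---|---|---|---|
| 35 | 0.63 | 47% | 59% | 12 points |
| 29 | 0.63 | 37% | 49% | 12 points |
| 35 | 0.5 | 26% | 37% | 11 points |
| 35 | 0.8 | 76% | 84% | 8 points |
| 35 | 1.1 | 98% | 99% | about 1 point |

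At n = 35 and d = 0.63:

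- The Holm figure is 47% with or without the per-content ANOVA gate.
- A single pair rises from about 59% to 67%.
- If the Group × Content interaction must also be significant, joint power rises from 39% to 48%.
- If all six pairs over both contents form one family, Holm over six gives about 37%. The closed test at 0.025 per content gives about 47%.

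**4. Familywise error** (n = 35):

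- Within one content, behind that content's own ANOVA, unadjusted pairs: about 5% under the full null and under partial nulls. The false CC–HC rate under hypothesis 1 at d = 0.63 is about 3% with Holm and 4.8% without.
- No per-content gate, t-tests opened by the interaction alone, EDR means equal and NED means far apart: 12.1% within EDR unadjusted, 4.1% with Holm over three.
- Both contents together, per-content gates at 0.05, unadjusted pairs: about 9% to 10%. Holm over six pairs gives about 5% or less.
- Both contents together, closed test at 0.025 per content: at or near 5%, as the bound 2 × 0.025 = 0.05 implies.

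**The case against.** A reader might infer that Holm here is a double correction that buys no error control and costs 12 points of power across hypotheses 1 and 2. The article does not support that reading.

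- **The gate.** The stated gate is a significant main effect or interaction in the 2 × 3 ANOVA. Post-hoc ANOVAs are planned, but the t-tests are not made conditional on them. If the interaction alone opens the t-tests, Holm does real work (12.1% against 4.1%). This stands.
- **The family.** If it spans both contents, Holm over six pairs holds an error rate that per-content testing at 0.05 would let rise to 9–10%. This stands against removing Holm outright, but not against the closed test at 0.025 per content.
- **The size.** Twelve points is joint power in one scenario. The article cites effects of d ≥ 1.5 for interpretation bias and d = 0.8 for ED-specific memory bias. The gain is about 8 points at 0.8, about 1 point at 1.1 and none at 1.5. This stands.
- **Status.** Holm after an omnibus test is a valid, standard choice and contradicts nothing in the article. A fuller plan may define the gate and family. This makes the point an efficiency gain, not the correction of an error.

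What survives the objection is that under either family a rule with the same 5% bound and more power is available.

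**Conclusion.** The point holds as a cheap improvement. The Holm rule is valid but more conservative than three groups require. It is redundant only when two conditions are both met: each content's t-tests depend on that content's own one-way Group ANOVA, and the family is the three pairs in that content. The article states neither.

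The benefit is largest at small to medium effects, roughly 8 to 12 points of joint power for d between 0.5 and 0.8 at 35 per group, and it fades at the large effects cited for interpretation bias. Against a six-pair Holm the gain is about 10 points at d = 0.63. The power figures depend on the assumed mean patterns and equal variances; those involving the interaction or both contents also depend on the assumed correlation of 0.5. The familywise result for three groups follows from closed testing and does not depend on the effect size or the mean pattern.

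**What to change.** Replace the Holm clause, for group comparisons only, with wording such as:

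> Within each content, the three pairwise t-tests are performed only if that content's one-way Group ANOVA is significant at 0.05, and each is then tested at 0.05 (closed testing, three groups). If error is to be controlled over both contents together, 0.025 is used per content for both the ANOVA and the t-tests.

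Choose one of the two levels before the data are analysed. Keep Holm for other sets of post-hoc tests. Do not delete Holm without writing in the per-content gate.

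The change takes a sentence or two and needs no further data or participants, because post-hoc ANOVAs are already planned. The price is a higher chance of a false CC–HC difference, which bears on hypothesis 1c; it remains within the nominal level.

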## Discussion

Dysfunctional cognitions including cognitive biases are known to characterize individuals with AN. However, less is known about the specificity of biases, i.e., if biases in AN patients occur only for ED-related information or also for non-ED-related emotional information (content-specificity) and if biases are unique to individuals with AN or are also shown by individuals with other mental disorders (disorder-specificity). The present study is designed to systematically assess cognitive biases in adolescents with AN on three levels of information processing (attention, interpretation, and memory) and with regard to two types of information (ED-related and non-ED-related information). To address not only content- but also disorder-specificity, adolescents with AN are compared not only to a healthy but also to a clinical control group [comprising adolescents with major depression, social anxiety, or generalized anxiety disorder, which are the most frequent comorbidities of AN; e.g., 44, 46].

We expect to find more pronounced negative cognitive biases on all three levels of information processing and for both types of content in adolescents with AN compared to healthy adolescents [in line with studies in adults; e.g., 11, 12, 20, 22, 29]. We expect the specificity of biases to translate as differential results for the two types of content with the AN group showing stronger biases for ED-related information but similar or less pronounced biases for non-ED-related information than the group of CCs [who are expected to show more pronounced biases for non-ED-related information; see 47, 48; but similar biases for ED-related information in comparison to the HC group].

The study focuses on 12–18-year-old adolescent girls as adolescence is the most common time for the onset of AN [e.g., 3] while also being a time in which major cognitive and affective development is ongoing [e.g., 37], making it difficult to transfer results obtained in adult populations on this age group. Insights about factors contributing to the maintenance of AN already at a relatively early stage may be particularly informative for interventions that step in early in the course of the disorder.

Major strengths of the study include a thorough diagnostic assessment of all participants, the systematic and comprehensive assessment of cognitive biases addressing multiple levels of information processing as well as the content-specificity hypothesis, and the inclusion of a clinical control group to also address the question of disorder-specificity. Furthermore, an elaborate data processing and analysis strategy has been decided upon beforehand.

Influential publications have underlined the importance of experimentally investigating key processes of psychopathology in EDs [87] and especially AN [88] as this may shed light on the mechanisms that cause and maintain the disorder as well as the mechanisms that need to be targeted in order to change and reduce ED psychopathology. Cognitive biases may be a promising starting point since they are both, presumably involved in the etiology and maintenance of AN [e.g., 8–10], as well as modifiable in experimental settings [e.g., 34, 40, 41, 89–91]. However, as also suggested by Paslakis and colleagues [57], precisely specifying what kinds of cognitive biases characterize patients with AN and investigating the extent to which these biases are related to their psychopathology is an essential precursor for efficiently experimentally modifying biases in this particular population. As attempting to manipulate cognitive biases only makes sense for biases that (1) characterize the target population (in comparison to control groups), (2) are related to their psychopathology, and (3) can be reliably measured, systematic knowledge on biases can help subsequent studies to choose the most promising ones as their interventional targets.

In summary, the present study, which is the first to assess cognitive biases in AN in such a comprehensive way, particularly in adolescents, is likely to advance our knowledge about an important maintaining mechanisms of AN and make a valuable contribution to the field. It will have important implications for cognitive behavioural theories of AN as well as subsequent studies aiming to modify cognitive biases in adolescent AN patients.^5^

